We hypothesize that the changes during the learning phase significantly differ between errorless and errorful learning conditions for (i) movement variability, (ii) perceived competence, and (iii) PFC activity. We further hypothesize that the changes across the same variables and task performance significantly differ from before to after practice between errorless and errorful learning conditions. Finally, we will test whether the changes in task performance from before to after practice are moderated by movement variability, perceived competence, or PFC activity.

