**Figure 2 fig2:**
[figure not shown]
Diagram of the overhand throwing task in the test phase.

The pretest will be conducted on the first experimental day, immediately prior to the first practice session. It will consist of one practice trial, followed by 10 trials without any instruction or feedback (apart from being told to aim for the highest score). The posttest will be conducted on the second experimental day, immediately following the second practice session. We will adopt an A-B-A design (retention-transfer-retention) as used in motor learning studies (Maxwell et al., 2017). The first retention test will evaluate performance after the training phase; the transfer test will verify whether cognitive resources are required to support motor performance; the second retention test will assess whether any difference in performance in the transfer test was due to continued learning. The retention tests will consist of one practice trial followed by 10 trials (i.e., identical to the pretest). The transfer test consists of 10 trials with a concurrent cognitive task of counting backward (e.g., Capio et al., 2013b). The counting backward task will vary as a function of differences in cognitive ability that are associated with age. Children are asked to count backward from 100 in one (e.g., 100, 99, 98…), whereas older adults are asked to count backward from a randomly selected starting point in three (e.g., 95, 92, 89…).

Procedures for monitoring protocol adherence will include the use of attendance logs and reminders before each block to encourage engagement. We expect minimal risk of dropouts because participation will be completed within two sessions. Nevertheless, missed appointments for the second session will be followed up and rescheduled within 2 days of the original schedule. Because post-tests will be administered in the second session, participants who completely miss the said session will be excluded from data analysis. There are no requirements regarding concomitant care, but participants will be asked to report any activities that involved a similar throwing task in the day(s) intervening the two study sessions. Any deviation from the protocol, including those due to technical issues, and related concomitant care will be documented for each participant.

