We will use random effects multilevel/hierarchical linear model (HLM) analysis to test our hypotheses. To test changes in the learning and test phases, we use the HLM approach to estimate growth curve models to examine change over time (i.e., practice blocks, test) on two levels—level one representing individual change over time and level two accounting for the extent to which change differs between age groups and between the EL and EF groups (Raudenbush and Bryk, 2002). The level one model will quantify individual changes in the measured variables (i.e., task performance, movement variability, perceived competence, PFC activity) as a function of time (i.e., practice block, test). Random slopes and intercepts will be specified for participants to account for individual differences in baseline performance and rate of change. For the level two model, fixed effects will include age group (i.e., children, older adults) and learning condition (i.e., EL, EF) as categorical predictors. Additional fixed effects will include the relevant covariates (i.e., cognitive processing speed and executive function). The random effects of the repeated measures estimate the relationship of the scores at the first time point to the rate of change over time. Planned interactions will include age group × learning condition to examine different effects of the learning condition across age groups and time × learning condition to test whether learning trajectories vary between the EL and EF conditions. Separate models will be fitted to each of the measured variables.

The statistical assumptions underlying HLM (i.e., normality of residuals, homoscedasticity, and independence of random effects) will be evaluated through diagnostic plots and residual analysis. If violations are detected, robust estimation methods or appropriate variable transformations will be applied. Missing data will be handled through maximum likelihood estimation under the assumption of missing at random (MAR) to retain all available data and minimize bias. Our data analysis approach is deemed appropriate because it allows us to track change over repeated measures and account for participants’ individual patterns of change by calculating estimates of within- and between-individual variation (O’Connell and McCoach, 2004).

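### The test-phase model estimates a free arm difference at pretest and has no pretest covariate, so the pre-to-post contrast is unbiased but less precise than it need be

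*Protocol article*

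**What the plan says.** The second hypothesis, in section 1.4 of the protocol article, is that "the changes across the same variables and task performance significantly differ from before to after practice between errorless and errorful learning conditions".

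Section 2.6 sets out the model used to test it:

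- Each measured variable is a level-one outcome modelled "as a function of time (i.e., practice block, test"), so the pretest is one of the outcome occasions.
- At level two, "fixed effects will include age group (i.e., children, older adults) and learning condition (i.e., EL, EF) as categorical predictors".
- The covariates named are two cognitive abilities, and the pretest value is not among them: "Additional fixed effects will include the relevant covariates (i.e., cognitive processing speed and executive function").
- On the random part of the model: "Random slopes and intercepts will be specified for participants to account for individual differences in baseline performance and rate of change".
- The planned interactions are age group × learning condition and "time × learning condition to test whether learning trajectories vary between the EL and EF conditions".

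Nothing in section 2.6 sets the EL and EF means equal at pretest. Section 2.1 describes stratified block randomisation to EL or EF within each age group. On timing, section 2.2 states: "The pretest will be conducted on the first experimental day, immediately prior to the first practice session".

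**The concern.** A randomised comparison with a true pre-intervention measurement can use that measurement to sharpen the arm contrast. Here the pretest is collected but spent on estimating an arm difference that is zero by design. The random intercept and slope may look like baseline adjustment. They describe variation between individuals and leave the fixed-effect contrast between arms unadjusted.

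The stake is precision. A chance pretest imbalance of δ shifts the unadjusted change contrast by −(1−ρ)δ through regression to the mean, whereas the adjusted contrast removes that shift. With 23 per arm (half of 46), the standard error of the pretest difference is √(2/23) = 0.29 SD, so an imbalance above 0.3 SD arises in about 31% of randomisations. With both age groups pooled (46 per arm) it is √(2/46) = 0.21 SD, or about 15%. The point concerns the pretest-to-posttest models and not the practice-block models.

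**Working it through.** **1. The plan's own figure.** Section 2.1 gives 46 per age group from a hierarchical linear regression with effect size 0.23, 80% power and alpha 0.05. Reading 0.23 as f² and assuming two tested predictors, a noncentral F test with λ = 0.23 × 46 = 10.58 has power 0.81, and 46 is the smallest N that reaches 80%. One tested predictor would give 37 and three would give 52. Allowing for 10% loss, 46/0.9 = 51.1, which rounds up to the 52 to be recruited. The 46 therefore reproduces, but from a regression effect size and not from the variance of a change score.

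**2. What time × condition estimates.** With a free condition effect and complete data:

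- Two occasions: in simulated mixed-model fits with age group and age group × condition, the coefficient equalled the raw difference in mean change to about 10⁻¹⁵.
- A generalised least squares check with correlated random intercept and slope, age group, age group × condition and a cognitive covariate gave 0.1129 for both quantities.
- Four occasions with linear time: the coefficient equalled the difference in mean individual slopes (0.0348 for both).

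The covariates enter as main effects and cancel from within-person change. The intercept–slope covariance does not alter the contrast.

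**3. Precision, one pretest and one posttest.** With equal variances σ² and correlation ρ, the variance is proportional to 2(1−ρ) for the change contrast and to 1−ρ² for the adjusted contrast. The ratio is (1−ρ²)/[2(1−ρ)] = (1+ρ)/2. The article gives no ρ, so the values below are assumptions.

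| ρ | 2(1−ρ) | 1−ρ² | variance ratio | standard error ratio |
|---|---|---|---|---|
| 0.3 | 1.4 | 0.91 | 0.65 | 0.806 |
| 0.5 | 1.0 | 0.75 | 0.75 | 0.866 |
| 0.7 | 0.6 | 0.51 | 0.85 | 0.922 |
| 0.9 | 0.2 | 0.19 | 0.95 | 0.975 |

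**4. Three posttests.** Section 2.2 has retention, transfer and retention tests, and section 2.6 does not say how they enter. Assume equal correlation ρ among all four tests:

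- Mean of the three posttests: unadjusted variance (4/3)(1−ρ), adjusted (1−ρ)(1/3+ρ), ratio (1+3ρ)/4. This is 0.475, 0.625, 0.775 and 0.925 at the four values of ρ.
- Linear trend over four occasions, with the arms constrained to be equal at pretest: ratio 0.60, 0.74 and 0.85 at ρ = 0.3, 0.5 and 0.7.

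The size of the loss changes, but its direction does not.

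**5. Power, under an added assumption.** Suppose the change contrast has 80% power at N = 46 (df 44, two-sided 0.05). The noncentrality is then 2.865. Divide it by √[(1+ρ)/2] for the adjusted contrast. For the pooled model, multiply by √2 to get 4.051 (N = 92, df 90).

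| ρ | one age group, adjusted (from 80%) | both age groups pooled, adjusted (from 98.0%) |
|---|---|---|
| 0.3 | 93.5% | 99.9% |
| 0.5 | 89.9% | 99.6% |
| 0.7 | 86.0% | 99.2% |
| 0.9 | 82.0% | 98.4% |

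For one age group alone, the gain reaches 5 points when ρ is about 0.75 or lower. In the pooled model it runs from 0.4 points (ρ = 0.9) to 1.9 points (ρ = 0.3).

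**The case against.** The strongest reply concerns size. Section 2.6 describes one model holding both age groups, with no three-way term, so time × condition draws on about 92 participants. On the same assumption that gives 80% at 46, the planned contrast already has about 98% power and little is left to gain. This stands. A reader might infer a gain of 5 points or more at ordinary correlations. The article supports that only if each age group is analysed alone, which its description of two experiments and its sample size per age group leave possible but section 2.6 does not plan. The 80% anchor is also not a change-score figure.

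It also stands that the identity with the change-score difference, and the match between the constrained model and pretest-as-covariate, need complete pairs. Section 2.6 uses maximum likelihood under missing at random, and section 2.1 allows for data loss. Pairs should be nearly complete for task scores, because participants who miss the second session are excluded. Sensor data may be less so.

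Three further replies do not hold:

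- That the hypothesis is about change: the adjusted contrast tests the same randomised difference with a smaller standard error.
- That this is detail for an analysis plan: the article itself lists the fixed effects, covariates, random effects and interactions.
- That random intercepts already account for baseline: step 2 of the working shows that they do not adjust the arm contrast.

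**Conclusion.** The point holds as one of efficiency. As written, the test-phase contrast is not adjusted for pretest and is less precise than an adjusted one for any ρ below 1. For one pretest and one posttest, the variance falls by 35%, 25%, 15% or 5% at ρ = 0.3, 0.5, 0.7 or 0.9. The power gain cannot be fixed from the article, which gives neither ρ nor a change-score variance.

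A reader might infer that the planned estimate is biased. It is not: under randomisation the change contrast is unbiased, and a chance imbalance affects a single trial's estimate without shifting its average.

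The conclusion rests on random allocation, on a pretest given identically to both arms before practice, and on equal pretest and posttest variances for the simple ratio. Staff are not blinded, but the pretest is given without instruction or feedback beyond aiming for the highest score, so a common pretest mean is reasonable.

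**What to change.** In section 2.6, state for the test-phase models of accuracy, movement variability, perceived competence and PFC activity that the EL and EF means are constrained to be equal at pretest within each age group. The condition and age group × condition terms then act only after practice, with a condition effect kept at each post-practice test. Keep the time structure, so that the moderation model at the end of section 2.6, which needs a pretest-to-posttest slope, can still be fitted.

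Alternatively, analyse the post-practice values with the pretest value of the same measure as a covariate. With complete pairs this gives essentially the same contrast. It drops participants without a pretest value and supplies no slope for the moderation model, so the constrained form fits this plan better.

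The cost is a change of wording: no new data, participants or software. It should be settled before outcomes are analysed.

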### Motor learning

1.1

Motor learning consists of internal processes associated with practice or experience that lead to relatively permanent changes in movement skill proficiency (Schmidt and Lee, 2020). Adams (1971) described motor learning as a problem-solving process in which movement errors are solved using cognitive resources. Thus, a cognitive process has long been considered an underlying factor in acquiring movement skills. For instance, in their seminal work, Fitts and Posner (1967) described cognitive, associative and autonomous stages of learning. During the initial cognitive stage, learners discover and use rule-based knowledge to monitor and control their movements. Movement strategies are refined during the associative stage, and subsequent performance has little reliance on rule-based knowledge during the autonomous stage. The cognitive stage has been suggested to require working memory resources to support the processing, storage, and manipulation of incoming sensory information (Maxwell et al., 2003).

With this understanding, movement skills are considered to be acquirable explicitly or implicitly (Masters, 1992). Movement skills that are learned explicitly are accompanied by the accumulation of declarative knowledge (i.e., rules, mechanics of movement) that is used to support motor performance (Maxwell et al., 2003). Movements that are learned implicitly do not necessarily require increased knowledge of rules and mechanisms to support performance, despite learners being aware that they are learning the movement(s) (Masters, 1992). For example, Maxwell et al. (2001) reported that implicit learners verbalized fewer rules related to motor performance than explicit learners did. Children have also been shown to accumulate more knowledge during explicit learning conditions (van Abswoude et al., 2020). With respect to the stages of motor learning, the cognitive phase appears particularly crucial in explicit but not in implicit motor learning. Age and intelligence (e.g., IQ), which are related to working memory capacity, have also been identified as individual factors that affect explicit, but not implicit, motor learning (Steenbergen et al., 2010).

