### Errorless motor learning

1.2

One approach to promote implicit motor learning is to minimize errors during practice, i.e., errorless motor learning. When learners experience practice errors, they seek—and test—alternative movement solutions, form rules to support movement performance, and consequently utilize working memory resources (Maxwell et al., 2001). This typically promotes explicit motor learning. In contrast, when learners experience fewer practice errors, they are less likely to utilize working memory resources to explicitly seek—and test—alternative movement solutions (Capio and Eguia, 2021). For instance, young adults learning a golf putting task actively modified their movements following unsuccessful performance, suggesting that experiencing practice errors involved hypothesis testing behaviors (Poolton et al., 2005). More recently, Banihosseini et al. (2025) reported that motor performance was unaffected by mental fatigue during errorless motor learning showing limited reliance on working memory.

Errorless motor learning promotes implicit learning by manipulating constraints, such as task difficulty. In the early stage of learning, movement training might begin with an easy task during which learners experience few practice errors (Capio and Eguia, 2021). Poolton et al. (2005) reported that early experiences of success during practice develop movement skills that tend to be independent of working memory, which is consistent with implicit motor learning. Early success in practice is critically important, and machine learning methods have shown that initial performance in skill learning strongly predicts final task performance (Abeles et al., 2023). Indeed, errorless motor learning has been consistently shown to improve movement outcomes, including gross motor skills (Capio et al., 2017) and novel sporting skills (Maxwell et al., 2017).

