### Participants and eligibility criteria

2.1

This study protocol was developed and reported following the updated Standard Protocol Items: Recommendations for Interventional Trials (SPIRIT) guidelines (Chan et al., 2025). The research consists of two experiments, which follow the same design but with adaptations to suit the developmental requirements of children and older adults.

Corresponding to the two experiments, the following participant groups will be formed: (i) children aged 6 to 8 years and (ii) older adults aged 60 years and older. For both participant groups, the inclusion criteria are as follows: (i) normal or corrected-to-normal visual acuity and (ii) no diagnosed neurodevelopmental, medical or orthopedic conditions that constrain the stability and mobility of the upper limb or trunk. For cognitive screening, children should not require support for special educational needs; older adults should score ≥ 24 on the Chinese version of the Mini–Mental State Examination. Owing to the task, those who are ambidextrous will also be excluded (see Procedures below for the task). We acknowledge that these exclusion criteria allow us to control the experimental conditions but limit the generalizability to populations without cognitive or physical impairments.

Using GPower 3.1.9.7 and assuming an analysis based on hierarchical linear regression, a sample size of 46 participants for each age group is needed to determine the effects of errorless and errorful learning conditions on movement performance. The parameters include an effect size of 0.23 based on improvement in task performance (i.e., number of successful hits) that differentiated errorless and errorful conditions among young adults that followed a similar protocol (Capio and Eguia, 2025), 80% power, and an alpha of 0.05. Because the procedures will take place over two sessions and fNIRS procedures may be uncomfortable and challenging to some, we will aim to recruit 52 participants per age group (i.e., ~10% additional) to mitigate the potential impact of sample attrition and/or data loss.

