To account for individual cognitive processing speed and executive function capacity, we will use the Color Trails Test (CTT)-1 and -2 (Williams et al., 1995) for children and the Trail Making Test (TMT)-A and -B (Bowie and Harvey, 2006) for older adults. CTT-1 and TMT-A scores are considered measures of visual search and perceptual speed, whereas CTT-2 and TMT-B scores reflect the task-switching component of executive function. For all participants, verbal working memory will be assessed using a backward digit span test (Ramsay and Reynolds, 1995), and visuospatial working memory will be assessed using a reversed Corsi block tapping test (Corsi, 1973).

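### The mixed models carry age only as children versus older adults; adding age in years and age × time would bring a small precision gain and protect the non-randomised moderator tests

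*Protocol article*

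**What the plan says.** Section 2.6 sets out the level-two model: "fixed effects will include age group (i.e., children, older adults) and learning condition (i.e., EL, EF) as categorical predictors". It continues: "Additional fixed effects will include the relevant covariates (i.e., cognitive processing speed and executive function". The list is introduced by i.e., so it reads as complete, and age in years is not on it. The planned interactions are age group × learning condition and time × learning condition. Each participant has a random intercept and a random slope. A further model in the same section tests whether the cognitive and affective process variables moderate the pretest-to-posttest change in performance.

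Section 2.1 defines the two participant groups as "i) children aged 6 to 8 years and (ii) older adults aged 60 years and older". Allocation within each age group is stratified by sex; age within the band is not a stratification factor.

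On age itself, section 1.1 starts from two personal characteristics: "Age and intelligence (e.g., IQ), which are related to working memory capacity". The same sentence goes on to report that both of these "have also been identified as individual factors that affect explicit, but not implicit, motor learning". Section 1.2 says of practice with errors: "This typically promotes explicit motor learning". Section 2.3 also measures working memory for everyone; for example, "verbal working memory will be assessed using a backward digit span test".

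**The concern.** Read together, sections 1.1 and 1.2 imply that age affects learning, and mainly under errorful practice. Neither the randomisation nor the model deals with age inside a band, although each participant's age has to be known to establish eligibility. Two things are at stake.

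- **Precision.** Any age-related spread within a band stays in the between-person variance.
- **Confounding of the moderator tests.** Movement variability, perceived competence and prefrontal activity are observed, not assigned. If age within a band drives both one of these and the gain in performance, an apparent moderation may partly be an age effect. Randomising the practice condition does not protect against this.

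**Working it through.** **1. The plan's own figure.** Reading the effect size of 0.23 as Cohen's f² (the metric is not named), with two tested predictors, alpha 0.05 and noncentrality 0.23 × 46 = 10.58, the power at N = 46 is 0.810, and 46 is the smallest N that reaches 80%. Allowing for 10% loss, 46/0.90 = 51.1, rounded up to 52. Both figures reproduce, and nothing in this point makes them wrong.

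**2. Inputs for the check.** The article gives no correlation between age in years and outcome and no variance components. Assumptions: 23 per cell (46 per age group, two arms); six occasions, as in blocks three to eight of one session; intercept variance 1, residual variance 1, slope variance 0.03; r is the within-band correlation of age with level and with slope. With time coded in unit steps and centred, the sum of squares of time is 17.5. Estimating the age slopes when age has no effect inflates the standard error by a factor of about 1.012.

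**3. Age group × condition** (a contrast of four cell means).
- Without age: variance per person = 1 + 1/6 = 1.167, so SE = √(4 × 1.167/23) = 0.450.
- With age: variance = (1 − r²) + 1/6, and SE ratio = √(new/1.167) × 1.012.

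**4. Time × condition** (46 per arm over both age groups).
- Without age: slope variance = 0.03 + 1/17.5 = 0.0871, so SE = √(2 × 0.0871/46) = 0.0616.
- With age as a main effect only: SE ratio 1.000, because a stable difference in level does not enter the person's slope.
- With age × time: variance = 0.03(1 − r²) + 0.0571, and SE ratio = √(new/0.0871) × 1.012.

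| Assumed r | Age group × condition, SE ratio | Time × condition with age × time, SE ratio |
|---|---|---|
| 0.1 | √(1.157/1.167) × 1.012 = 1.008 | √(0.0868/0.0871) × 1.012 = 1.010 |
| 0.3 | √(1.077/1.167) × 1.012 = 0.972 | √(0.0844/0.0871) × 1.012 = 0.996 |
| 0.5 | √(0.917/1.167) × 1.012 = 0.897 | √(0.0796/0.0871) × 1.012 = 0.967 |

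The coding of time matters a little. With time counted from the first occasion, generalised least squares gives a reduction for age group × condition of about 2–3% at r = 0.3 and 9% at r = 0.5 with age alone, and about 3% and 10% once age × time is added.

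**5. Sensitivity to the variances.** Mixed models were also simulated for one age group (46 participants, six occasions, 60 replicates) with more slope variance relative to noise. The time × condition SE was 0.0609 with and without an age main effect, even at r = 0.5 with level. Adding age × time took it from 0.0609 to 0.0593 (2.6% lower) when r with slope was 0.3 in both arms. When age acted only in the errorful arm, age × time took it from 0.0633 to 0.0635 at r = 0.3 and from 0.0629 to 0.0617 (1.9% lower) at r = 0.5. Whatever the variances, the reduction at r = 0.3 cannot exceed 1 − √0.91 = 4.6%, before the cost of estimating the age slopes.

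**6. Moderator model.** No figure can be put on the confounding, because the article gives no association of age with the moderators or with change. The tested quantity is a moderator × time effect, so age has to enter as age × time to compete with it; a main effect of age would not.

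**The case against.** The case for leaving the model alone is substantial.

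- Age group is the design factor of two parallel experiments, not a continuous scale cut in two, so nothing in the text is an error or a contradiction. This stands. The point is an improvement, not a correction.
- The article links the age effect to working memory, and it measures processing speed, task switching and working memory. This stands in part: the cognitive covariates will absorb some of the age effect. But section 2.6 names only processing speed and executive function and does not say that the digit span and Corsi scores enter. Age could also act through physical capacity, which section 2.2 raises when discussing throwing distance and which the cognitive tests do not measure.
- The random intercept already handles stable differences in level. This stands for time × condition, as step 4 shows. It does not hold for age group × condition, whose error contains the intercept variance.

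Two stronger readings are tempting, and the article supports neither. A reader might infer that chance age imbalance biases the condition comparison. With 26 per arm, the difference in mean age has a standard deviation of √(2/26) = 0.277 within-band SDs, and an imbalance above 0.3 SD occurs about 28% of the time. That is true of any unadjusted covariate. Randomisation keeps the comparison unbiased, and the test's error rate already allows for chance imbalance. A reader might also infer a saving of about 5 to 15 participants per age group, from 46/(1 − r²) − 46 at r = 0.3 and 0.5. That formula belongs to a single-outcome regression with assumed correlations, not to the planned growth models.

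**Conclusion.** The point holds as a minor one. Section 2.6 fixes a list of predictors that leaves out a baseline value known for everyone, which section 1.1 says matters for explicit learning.

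For the randomised comparisons the gain is precision only. At an assumed r of 0.3 to 0.5, the standard error is about 2–9% lower for age group × condition (3–10% with age × time) and about 0.4–3% lower for time × condition. At r = 0.1 it is unchanged or about 1% higher. These ranges rest on the illustrative variances in the working and on correlations that the article does not supply. The relevant r is the one left after the cognitive covariates, and within a 6-to-8-year band it may well be at the low end. The result does not show that a predictor is wasted or that the sample size is wrong.

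For the moderator tests the reason is different: age × time removes one plausible confounder of variables that were not randomised. The size of that confounding is unknown.

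**What to change.** In section 2.6, add age in years, centred within age group and with a separate slope per age group, to the level-two equations for both the intercept and the time slope (age and age × time). Do this in all models, including the cross-level moderator model. Prespecify age × time × condition as a sensitivity analysis, because sections 1.1 and 1.2 together imply that age acts mainly under errorful practice.

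The cost is a sentence or two of analysis text and about four degrees of freedom (two age slopes on the intercept, two on time), with more in the sensitivity analysis. Some of the gain will overlap with the cognitive covariates. No new data are needed, and fixing the adjustment before analysis also avoids a later data-driven choice about age.
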